## Methods

### Study design

A cluster randomized controlled trial including an effect-, process- and economic evaluation will be conducted in a minimum of 20 hospitals in the Netherlands using EPO and/or perioperative blood salvage in THA and TKA. Per hospital a representative orthopedic surgeon will be invited to participate in the study (see Additional file 1 for CONSORT checklist); consent of hospitals willing to participate will be gathered according to local hospital regulations. To prevent contamination bias, randomisation will take place at the hospital level stratified by geographic location of the hospitals. Randomisation will be performed by an independent researcher using a computer generated randomisation table concealed in a sealed envelope. The randomisation result will be revealed to the investigators and participating hospitals after the baseline measurement on effect outcomes takes place.

This trial compares:

1. The tailored strategy to de-implement use of EPO and perioperative blood salvage, and

2. A control strategy.

See Figure 1 for a flow-chart of the study design.

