#### Evaluation and outcome measures

1. Effect evaluation

The effect of the tailored strategy will be compared with the control strategy before and after carrying out the strategy. Outcomes will be measured at patient level, using retrospective medical record review at least three weeks postoperative with standardized registration forms. Measurement periods last for five months. Within each month, medical records of at least 10 consecutively treated patients will be reviewed in each participating hospital, with a maximum of 20 patients per month (depending on the number of patients treated within that month).

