### Statistical analysis

All data will be entered and stored in an electronic database. Descriptive statistics include frequencies, percentages, medians, means and SDs. Hospital and patient characteristics of study hospitals will be compared using t-tests and non-parametric tests (Mann-Whitney U test) for continuous variables and χ^2^-test for proportions. The overall effect of the intervention will be evaluated by comparing the average outcome in the control hospitals with the average outcome in the intervention hospitals. The effects on the percentage of patients receiving a THA or TKA in which BSMs (stratified to the % patients with EPO and % patients with perioperative blood salvage) are applied will be adjusted for clustering of patients in hospitals. Therefore, multilevel logistic regression analysis will be performed. Analyses will be based on the intention to treat principle, meaning that all participating hospitals will be included in the study arm (control or intervention) to which they are originally assigned, regardless of whether they participated in the components of the tailored strategy.

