### Sample size

We expect to detect an absolute difference of at least 20% in BSM use between the group receiving the de-implementation strategy and the control group. We assume that frequent BSM use, as assessed in the Dutch survey [25], means that BSMs are applied in 50% of the patients. To detect a difference of 20% (from 50% to 30%), with alpha 0.05, a two-sided testing and power of 80%, an intra-cluster-correlation coefficient of 0.08, 50 patients per hospital and 20 hospitals are needed (total of 1,000 patients). Given the 70% of hospitals in The Netherlands frequently applying BSMs [25], this means that 69 hospitals are eligible for the present study. Since the average hospital performs about 550 total hip and knee arthroplasties per year, it is feasible to include 20 hospitals and at least 50 patients per hospital in 5 months, before and after the intervention period.

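### With as few as 20 hospitals, usual large-sample inference from the planned multilevel logistic model would not hold the 5% error; one small-sample method should be fixed in advance

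*Protocol article*

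**What the plan says.** Under Study design, hospitals are randomised, stratified by geographic location, and the trial "will be conducted in a minimum of 20 hospitals in the Netherlands". The Sample size section sets the error rates ("with alpha 0.05, a two-sided testing and power of 80"%), the effect ("To detect a difference of 20% (from 50% to 30"%) and "an intra-cluster-correlation coefficient of 0.08", and concludes that "50 patients per hospital and 20 hospitals are needed (total of 1,000 patients").

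The Statistical analysis section describes the overall effect as "comparing the average outcome in the control hospitals with the average outcome in the intervention hospitals". It says the effect on use of blood saving measures will be adjusted for clustering, and then: "Therefore, multilevel logistic regression analysis will be performed". It gives no estimator, test statistic, reference distribution or degrees of freedom for this comparison. It neither specifies nor rules out a small-sample correction.

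**The concern.** A random hospital intercept accounts for the correlation between patients of one hospital. It does not by itself account for having few hospitals. The effect of arm is a contrast between hospitals, so its precision depends on a between-hospital variance estimated from about 20 units. Two features of ordinary maximum-likelihood inference then act in the same direction. The variance estimate is biased downward, because it does not allow for the fixed effects estimated at hospital level. The test statistic is also referred to the normal distribution, when something close to t with 18 degrees of freedom applies.

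At stake are the p-value and confidence interval for the trial's main claim. Under that form of inference a false-positive risk of about 1 in 13 (1/13 = 7.7%) would be reported as 1 in 20, with an interval too narrow to match. Reviewing more records per hospital does not help.

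**Working it through.** **Inputs from the article.** Two-sided alpha 0.05; power 80%; 50% versus 30%; intra-cluster correlation (ICC) 0.08; 50 patients per hospital; 20 hospitals as a minimum (Sample size, Study design). The upper limit per hospital follows from "with a maximum of 20 patients per month" over five months: 20 × 5 = 100.

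**Assumptions not in the article.** Ten hospitals per arm, equal numbers per hospital, post-intervention data only, no adjustment for baseline or strata.

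**1. The stated size reproduces.**
- Patients per arm without clustering: [1.960 × √(2 × 0.4 × 0.6) + 0.842 × √(0.25 + 0.21)]² / 0.20² = 93.
- Design effect: 1 + 49 × 0.08 = 4.92.
- 93 × 4.92 = 457.6 per arm; 457.6 / 50 = 9.15 hospitals, rounded up to 10 per arm. That is 20 hospitals and 1,000 patients, as stated.

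**2. Power with 18 degrees of freedom.**
- Standard error of the difference: √(0.46 × 4.92 / 500) = 0.0673, so the standardised effect is 0.20 / 0.0673 = 2.97.
- Power is 84.4% with the normal reference (83.4% with the pooled formula) and 80.3% with t on 18 df. Rounding up to whole hospitals supplies the margin.

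**3. Analytic approximation to type I error.**
- Normal cut-off where t(18) applies: P(|t₁₈| > 1.96) = 6.6%.
- With the maximum-likelihood variance also too small by 18/20: P(|t₁₈| > 1.96 × √(18/20)) = P(|t₁₈| > 1.859) = 7.9%.
- The same formula gives 7.6% at 22 hospitals, 7.4% at 24, 6.9% at 30 and 6.4% at 40.

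**4. Simulation under no effect.** 4,000 trials per row; random-intercept logistic model by maximum likelihood with adaptive quadrature. The Wald standard error holds the random-effect SD at its estimate. Monte Carlo standard error is about 0.4 points. Entries are rejection rates (%) at nominal 5%. The reference for Wald t is t on hospitals minus 2 df.

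| Setting | Wald z | Likelihood ratio | Wald t | t-test on hospital proportions |
|---|---|---|---|---|
| 20 hospitals × 50, rate 50%, ICC 0.08, beta-binomial | 7.4 | 6.1 | 5.4 | 4.4 |
| Same, logistic-normal (ICC on latent scale) | 7.9 | 6.8 | 6.1 | 4.9 |
| Rate 30%, beta-binomial | 8.3 | 7.2 | 6.6 | 5.4 |
| 100 per hospital, rate 50%, beta-binomial | 8.0 | 7.1 | 6.4 | 5.6 |
| ICC 0.30, rate 50%, beta-binomial | 8.6 | 7.1 | 6.4 | 5.9 |
| 40 hospitals × 50, rate 50%, ICC 0.08, beta-binomial | 5.9 | 5.4 | 5.2 | 4.6 |

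Two further simulations of 20 hospitals × 50 agree. One gave 7.6% for Wald z, 6.3% with t(18) and 4.5% for the hospital-level t-test. The other gave 7.8%, 6.1% and 5.0% at ICC about 0.08, and 7.9%, 5.8% and 5.0% at ICC about 0.22.

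**5. What the correction does to the interval.** Replacing 1.960 by the t(18) quantile 2.101 widens it by 2.101 / 1.960 = 1.07. Removing the variance bias as well multiplies by √(20/18) = 1.054, so about 1.13 in all.

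**The case against.** The strongest objection is that the article commits to a model class and not to a test. Multilevel logistic regression is a sound model for a cluster-randomised binary outcome, and every small-sample method proposed here fits within the sentence as written or can stand beside it. The wording about comparing hospital averages would even allow a hospital-level test. Choice of test and degrees of freedom is usual content for an analysis plan, which is not shown, so silence in a condensed article is not an error.

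A reader might therefore infer that the trial tests its primary outcome at 8% instead of 5%. The documents do not support that. Depending on the test, simulated rates at 20 hospitals run from about 4.4% to 8.6%, and 8% belongs to uncorrected maximum likelihood with a Wald z-test. Twenty is also a floor, with 69 hospitals said to be eligible. An analysis using baseline data, geographic strata or unequal numbers per hospital was not simulated, so its exact rate is not known. A reader might also infer that the trial is too small; the 80.3% power with 18 df shows otherwise.

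All of this stands and makes the point conditional, but does not remove it. The article does fix the pairing of model and minimum number of hospitals, and at 20 hospitals both ordinary large-sample tests for that pairing exceed 5% in every setting tried. The same section names the tests for comparing hospital and patient characteristics, so detail at that level was not wholly deferred.

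**Conclusion.** The concern holds in conditional form. If the planned model is used with the usual large-sample inference and only 20 hospitals, two-sided type I error is about 7.5 to 8% for maximum-likelihood Wald z and about 6 to 7% for the likelihood-ratio test on the plan's own inputs (up to 8.6% and 7.2% in the other settings tried). The excess falls as hospitals are added but is not gone at 30 (about 6.9% by approximation for Wald z) or 40 (about 6.4% by approximation, 5.9% simulated). This rests on equal arms, equal numbers per hospital and post-intervention data without covariates. It is a worthwhile, inexpensive improvement to the stated analysis. It does not show that the planned test is invalid, and it leaves the sample size standing.

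**What to change.** Keep the multilevel logistic model for estimation, and add one sentence naming a single small-sample method for the primary test and interval. If the analysis plan already names one, confirm that it does. In order of preference:

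- a hospital-level analysis with t on hospitals minus estimated parameters, or a permutation test that respects the geographic strata of the randomisation;
- otherwise restricted pseudo-likelihood with Kenward-Roger degrees of freedom.

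Referring the maximum-likelihood Wald statistic to t(18) is only a partial remedy: it still gave about 5.5 to 6.5% at 20 hospitals. The hospital-level t-test gave 4.4 to 5.6% in all 20-hospital settings except ICC 0.30 in beta-binomial data, where it gave 5.9%.

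The cost is a somewhat wider interval (about 7 to 13% relative to Wald z by step 5 of the working). Power remains about 80% on the plan's inputs, so no extra hospitals are needed. Fitting strata uses some of the 18 degrees of freedom, so their number, which the article does not give, should be kept small or taken into account. The Trial status section says that the intervention period was still running in March 2014, so on that timeline the method could be fixed before post-intervention data exist.

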### Sample size

We expect to detect an absolute difference of at least 20% in BSM use between the group receiving the de-implementation strategy and the control group. We assume that frequent BSM use, as assessed in the Dutch survey [25], means that BSMs are applied in 50% of the patients. To detect a difference of 20% (from 50% to 30%), with alpha 0.05, a two-sided testing and power of 80%, an intra-cluster-correlation coefficient of 0.08, 50 patients per hospital and 20 hospitals are needed (total of 1,000 patients). Given the 70% of hospitals in The Netherlands frequently applying BSMs [25], this means that 69 hospitals are eligible for the present study. Since the average hospital performs about 550 total hip and knee arthroplasties per year, it is feasible to include 20 hospitals and at least 50 patients per hospital in 5 months, before and after the intervention period.

### Ethical approval

The Medical Ethical Committee of the Leiden University Medical Center decided that ethical approval was not required under Dutch National law for this type of study (CME 13/132). The gathering of patient data will be conducted in compliance with the Good Clinical Practices protocol and Declaration of Helsinki principles [41].

### Trial status

The LISBOA II study started in March 2013. The preparation of the study components and the recruitment of hospitals to participate in the study were completed in September 2013. The baseline data collection in all hospitals was performed from September 2013 until January 2014. Currently (March 2014), the intervention period is ongoing.

## Discussion

The goal of this study is to test a tailored strategy to let physicians stop using EPO and perioperative blood salvage in primary elective THA and TKA, *i.e*., the de-implementation of non-cost-effective BSMs. This study is the next step following a RCT on EPO and perioperative blood salvage as transfusion alternatives in THA and TKA using a restrictive transfusion policy, showing that use of these BSMs is not cost-effective [18,19], and a study in which a tailored de-implementation strategy was systematically developed [25,30,34]. Given the large number of THA and TKA performed annually in the Netherlands and worldwide, de-implementation of non-cost effective BSMs contributes to more efficient healthcare.

A strength of this study is that it is one of the first studies that assesses the effect of a de-implementation strategy. The study results will thus lead to generalizable knowledge regarding de-implementation strategies of non-cost-effective interventions and how this differs from strategies for implementation. This knowledge is useful to contain healthcare spending and optimize outcomes [26,27].

A possible limitation of the study is the awareness of the study purpose among physicians within the control group. During the recruitment of hospitals for participation in our study, hospitals cannot be blinded to the aim of this study. Physicians want to know the study goal before giving approval for participation in a study. As a consequence, physicians of control hospitals are actively made aware of the fact that they deliver non-efficient care and thereby can make changes in their blood management policy. This does not resemble ‘standard practice’ in hospitals not participating in a study and may lead to a smaller difference in the effect between the intervention and control hospitals. We will try to limit this awareness by asking the study coordinators of each participating hospital not to inform their staff members (orthopedic surgeons and anesthesiologists) about the study.

A second limitation is bias as a result of local initiatives to optimize care for THA and TKA during the intervention period. For example, the implementation of ‘fast track’ or ‘joint care’ programs for THA and TKA may lead to abandoning perioperative blood salvage because of logistic reasons. Therefore, information on local, non-study related changes will be additionally inquired during the process evaluation.

Our study will not only demonstrate whether a tailored strategy to de-implement BSMs is effective, feasible and cost-effective compared to the control strategy, but will also contribute to general knowledge regarding differences between de-implementation and implementation strategies. Little is known about strategies to effectively de-implement common practices, for instance, whether de-implementation strategies should also be constructed following the same theoretical models and frameworks as implementation. It is likely that it is far more attractive for clinicians to implement something new than to de-implement something expensive or ineffective [26,27]. Our study will thus not only assess whether a tailored strategy to de-implement BSMs is effective, feasible and cost-effective compared to the control strategy, but will also contribute to general knowledge regarding differences between de-implementation and implementation strategies.

## Abbreviations

BSMs: Blood saving measures; EPO: Erythropoietin; THA: Total hip arthroplasty; TKA: Total knee arthroplasty; RCT: Randomized controlled trial; LISBOA: Leiden implementation study of blood transfusion management in hip and knee arthroplasties; TDF: Theoretical domains framework; CME: Medical ethics committee (in Dutch: Commissie medische ethiek); SDs: Standard deviations; BMI: Body mass index; ASA classification: American society of anesthesiologists classification; Hb: Hemoglobin.
